#### Functional secondary criteria and quality of life

At 1 year after randomization (8+/−2 months after 131I administration): percent of patients with persistent hypoparathyroidism and/or persistent vocal fold paralysis; subjective dysphonia (Voice Handicap Index, VHI) and dysphagia (SWAL-QOL) (questionnaires in their validated French versions) compared between groups

The Voice Handicap Index is composed of 10 self-administered questions relating to the functional, physical, and emotional aspects of voice. A French version has been validated [45].

The SWAL-QOL questionnaire is composed of 44 questions concerning eating difficulty, eating duration, eating desire, food selection, fear, and social impact. The validated French version requires approximately 20 min to complete [46].At 1, 3, and 5 years after randomization: Quality of life (SF36 + EuroQol EQ-5D), Anxiety (State-Trait Anxiety Inventory-STAI) [47–49].

The SF-36 is the short-form health survey with 36 questions. It yields an 8-scale profile: physical functioning, physical condition, bodily pain, general health, vitality, social functioning, emotional status, mental health, and psychometrically based physical and mental health summary measures [47]. It has been shown to be sensitive for evaluating changes in quality of life in thyroid cancer patients [55]. It can be self-administered in 5–10 min with a high degree of acceptability. The version used in the present study is the version which has a recall period of 1 week. This questionnaire has been employed in a previously published randomized controlled trial on thyroid cancer [40, 55].

EuroQol EQ-5D consists of 5 questions (each with 3 levels of responses) and a self-evaluation of health on a visual analog scale (0–100) [48]. It is employed for the calculation of the utility score for the calculation of QALY (quality-adjusted life years) in cost-utility analysis.

Anxiety will be measured using the Spielberger STAI questionnaire [49]. The STAI state is an instrument for measurement of anxiety. It has 20 questions with four possible responses to each question. Higher scores correspond to higher levels of anxiety. It is suitable for self-administration.

### Outcomes: Cost-utility analysis

A *cost-utility analysis* will be performed to compare total thyroidectomy to total thyroidectomy with bilateral prophylactic central neck dissection. The protocol used will be similar to the one used in ESTIMABL 1 trial and recently published in the Journal of Clinical Oncology [55]. The hypothesis is that TT alone and TTT + PND may differ in terms of the number of patients in complete remission at 1 year or in the number of patients requiring treatment of complications because of recurrent laryngeal nerve injury or hypoparathyroidism.

The horizon time will depend on the results obtained on the main criteria (1 year). If the study confirms the non-inferiority of TT versus TT + PND in terms of oncologic events, a horizon time of 1 year following the initial surgery will be considered.

Consequence will be expressed in QALYs (quality-adjusted life years). Utility score will be assessed using the EQ-5D questionnaire at baseline, 1, 3, and 5 years. QALY will be calculated by multiplying the length of time between two questionnaires by utility score.

Costs will be evaluated from the French collective perspective. Resources consumed by the patient’s management in each strategy will be collected prospectively at baseline, 1, 3, and 5 years.

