#### Data collection

Resource consumption collected will concern the following direct medical costs for:Hospitalization for initial surgery, including the time in the operating room and for performing the surgeryHospitalizations for management of complications (vocal fold paralysis, hypoparathyroidism)Hospitalizations for further treatments (surgery or iodine administration)Equipment, consultations, medical or paramedical acts for management of complicationsOther direct or indirect costs that are not expected to differ between strategies will not be collected.

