Secondary outcomes s1Unstimulated thyroglobulin levels between groups will be compared between groups using a chi-square test.The rate of patients in complete remission at 3 and 5 years will be compared between groups using a chi-square test.The rate of patients in with structural incomplete response, biological incomplete response, indeterminate response, distant metastases, or further treatments at 1, 3, and 5 years will be compared between the 2 groups using a chi-square test for each type of response.

For these secondary criteria we expect, based on retrospective series comparing the two surgical techniques (total thyroidectomy alone or total thyroidectomy + PND), rates of incomplete response or re-treatement in the range of the following:Difference in locoregional control = 6.9% at 10 years [1]Difference in rate of recurrence = 4.6% at 3 years [2]Difference in rate of retreatment = 8.2% at 5 years [3]Rate of structural recurrence = 1.4% at 8 years [44]The rate of patients at 1 year with persistent hypoparathyroidism requiring medication and/or with persistent vocal fold paralysis will be compared between groups using a chi-square test; subjective dysphonia (Voice Handicap Index) and subjective dysphagia (SWAL-QOL) toxicities will be compared using a Student test for each time of evaluation (or a Kruskall-Wallis non-parametric test if they are not normally distributed).Quality of life and anxiety: The investigator will inform the patient on the objective of QoL data collection. QoL data may be not exploitable in case of great number of missing questionnaires. Data will be analyzed according to the scoring manual of each questionnaire. A longitudinal analysis using a mixed model will be used to take into account of repeated QoL assessment and the initial value. If this analysis shows a significantly different effect between groups or an interaction between treatment and time, an analysis of the treatment effect on quality of life will be carried out at each time. Mean sub-scale scores will be compared using a Student test for each time of evaluation (or a Kruskall-Wallis non-parametric test if they are not normally distributed).

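### The cost-utility horizon depends on the primary result: 1 year if non-inferiority is confirmed, none stated otherwise, although costs and utilities are collected to 5 years

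*Protocol article*

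**What the plan says.** The rule is in the protocol article under Outcomes: Cost-utility analysis, and is repeated in the same terms under Health Economics Analysis. It opens with "The horizon time will depend on the results obtained on the main criteria (1 year"), and continues: "If the study confirms the non-inferiority of TT versus TT + PND in terms of oncologic events", then "a horizon time of 1 year following the initial surgery will be considered". Neither section gives a horizon for the case where non-inferiority is not confirmed.

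The same sections set out a longer data collection. On utilities: "Utility score will be assessed using the EQ-5D questionnaire at baseline, 1, 3, and 5 years". On costs: "Resources consumed by the patient’s management in each strategy will be collected prospectively at baseline, 1, 3, and 5 years". The cost items under Data collection include "Hospitalizations for further treatments (surgery or iodine administration").

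Under Statistical methods, Secondary outcomes, the protocol lists the differences it expects from retrospective series, among them "Difference in rate of retreatment = 8.2% at 5 years".

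**The concern.** A time horizon should be long enough to hold the costs and health effects in which the two strategies may differ. Here its length is set by the outcome of another analysis. Non-inferiority on excellent response at 1 year says that the remission rates lie within 5 points at that time. It does not say that retreatment, costs or quality-adjusted survival are equal from year 1 to year 5.

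The rationale for the choice of comparators says that a non-inferior result could lead to prophylactic dissection being abandoned, and that the cost-utility analysis may then show a benefit of the lesser surgery. This is the scenario in which the economic comparison is confined to 1 year. Later retreatment may count against thyroidectomy alone. The continuing cost and utility loss of persistent complications may count against dissection. A 1-year horizon cuts off both, and the reader could not tell which way the balance moves.

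**Working it through.** The protocol states no figure that this rule should reproduce, so the check sets its sections side by side and adds one calculation for scale.

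**1. What the rule does in each case.**

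| Primary result | Horizon stated | Data used, of those listed for the cost-utility analysis |
|---|---|---|
| Non-inferiority confirmed | 1 year after surgery | Baseline and 1 year |
| Not confirmed | None | Cannot be determined |

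In the first case, two of the four listed time points enter the analysis (baseline and 1 year, not 3 and 5 years), and 1 of 5 years of planned follow-up (1/5 = 20%).

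**2. Whether another planned analysis makes up for it.** The planned sensitivity analyses vary individual costs, incidence of events and utilities, and bootstrap the incremental ratio. None varies the horizon, and no second horizon is planned in the text shown.

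**3. Whether the trigger justifies the cut.** The trigger is worded as non-inferiority in oncologic events. The primary criterion is excellent response at 1 year, which the protocol itself calls a surrogate endpoint, with a margin of 5 percentage points. Neither the endpoint nor the margin speaks to resource use or utility after year 1.

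**4. Whether the protocol expects anything after year 1.** It does.
- It justifies follow-up to 5 years by a study in which 81% of recurrences occurred within 5 years (77% of structural recurrences in a second study).
- It lists expected differences of 4.6% in recurrence at 3 years and 8.2% in retreatment at 5 years.
- It measures persistent hypoparathyroidism and vocal fold paralysis at 1 year. These complications arise within the 1-year horizon, but where they persist their cost and utility loss continue beyond it.

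**5. Scale.** Inputs: 299 per group (Determination of sample size) and the two expected differences (Secondary outcomes), read as absolute percentages.
- Retreatment by 5 years: 0.082 × 299 = 24.5, about 25 more retreated patients in one arm than in the other.
- Recurrence by 3 years: 0.046 × 299 = 13.8, about 14.

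Both are between-arm differences counted from time zero. The part arising in year 1 would be inside a 1-year horizon, and the documents do not give it. The excess after year 1 could therefore lie anywhere from about 0 to 25 for retreatment, assuming that the year-1 difference does not run the other way.

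**The case against.** **The rule is written in advance.** A reader might infer that the horizon will be picked freely once the result is known. The text does not support that for the non-inferior case, where 1 year is named. The horizon depends on the result without being a post hoc choice. Only the other branch is open.

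**The later data are not thrown away.** A reader might infer that the 3- and 5-year data are discarded. They are not: EQ-5D at 1, 3 and 5 years is also a quality-of-life outcome, and further treatment at 1, 3 and 5 years is a secondary oncologic criterion. The data go unused only in the cost-utility analysis. The verb in the rule (considered) is also soft and does not forbid a further horizon. It does not plan one either.

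**One year has a rationale.** The protocol expects the strategies to differ in remission at 1 year or in treatment of complications, and complications appear within the first year. This stands as a reason to report a 1-year analysis, and a 1-year result is available sooner. It does not cover the continuing burden of persistent complications, or later retreatment, which the protocol itself lists as a cost.

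**The 8.2% may overstate the matter.** It comes from retrospective series. The same list gives a structural recurrence rate of 1.4% at 8 years, and Table 1 cites a meta-analysis of randomized studies with 2.5% against 2.7%. The 8.2% is also not conditional on a non-inferior result, and the list does not say which arm it disfavours; the same source is cited elsewhere in the article in support of dissection, so reading it as against thyroidectomy alone is an inference. All of this stands. The later difference may be small, and a 5-year analysis would show whether it is.

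**Unseen detail.** The economic methods are said to follow those of an earlier trial of the network, and detail such as discounting may sit in a fuller document. That is not criticised here. The horizon rule is stated in the article, twice, and can be judged as stated.

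**Conclusion.** The point holds as a minor one about a secondary analysis. The primary comparison is untouched. The horizon is conditional on the primary result, one branch has no horizon, and the branch that is defined leaves the 3- and 5-year costs and utilities out of the cost-utility analysis without a reason that covers them.

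In time, the analysis would use 1 of 5 years of collected data. In patients, about 25 per 299 is an upper bound on the between-arm excess in retreatment. It rests on a cumulative figure from retrospective series, read as an absolute difference. The share after year 1 is not given, so 25 should not be read as the number of patients missed. The net direction of the effect on the cost-utility result is unknown.

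Nor do the documents support saying that the economic conclusion turns on a p-value. Non-inferiority is judged by a confidence limit against −5%, and that decision sets the horizon; whether the economic conclusion would change at 5 years is not shown.

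**What to change.** Under Outcomes: Cost-utility analysis and under Health Economics Analysis, replace the conditional sentences on the horizon with a fixed rule, for example: *The cost-utility analysis will be reported at horizons of 1 year and 5 years after initial surgery, whatever the result on the primary criterion, using the EQ-5D and resource data collected at baseline and at 1, 3 and 5 years.* This also settles the branch that now has no horizon.

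No new data, visits or patients are needed, since follow-up already runs to 5 years after the last randomization. The cost is some extra analysis and time. The primary analysis falls 1 year after the last randomization, so the 5-year economic result would follow about 4 years later (5 − 1 = 4). The 1-year result can still be reported on the present schedule.

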Viola D et al JCEM 2015 [34]	Propsective randomized single center	181 93 PND 88 TT	No difference in LRR (7.5% vs 8.0%)	More RAI in TT alone group (*p*=0.002)	Higher rate of permanent hypoPTH in PND group (*p*=0.02)
Chen L et al World J Surg 2018 [26]	Meta-analysis of retrospective studies	18,376 11,098 PND 5583 TT	Lower LRR in PND group 2.52% vs 4.59% (OR=0.65)		Higher rates of temporary (OR=2.23)and permanent hypoPTH (OR=2.22)and temporary VFP (OR=2.03)
Liang J et al Acta Otorhino Ital 2017 [35]	Meta-analysis of retrospective studies	6823 3312 PND 3511 TT	Lower LRR in PND group (*p*<0.01)		Higher rate of temporary (*p*<0.01) and permanent (*p*<0.01) hypoPTH and temporary VFP (*p*=0.023) in PND group
Zhao W et al Ann Surg Oncol 2016 [36]	Meta- analysis of retrospective studes	4437 1969 PND 2468 TT	Lower LRR in PND group 1.1% vs 3.4% (*p*=0.002)	More RAI in PND group 74.6% vs 59.9% (OR 1.20)	Higher rates of temporary (*p*<0.00001) and permanent (*p*=0.03) hypoPTH
Wang TS et al Ann Surg Oncol 2013 [6]	Meta- analysis of retrospective studes	1740 745 PND 995 TT	No difference in LRR		No difference in rates of permanent complcations
Lang BH et al Thyroid 2013 [7]	Meta-analysis of retrospective studies	3331 1592 PND 1739 TT	Lower LRR in PND group 4.7% vs 8.6% (OR=0.65)	More RAI in PND group 71.7% vs 53.1% (OR=2.60)	Higher rate of temporary hypoPTH PND group 26% vs 10.8% (OR=2.56)
Zetoune T et al Ann Surg Oncol 2010 [37]	Meta-analysis of retrospective studies	1264 396 PND 868 TT	No difference in LRR (2.02% vs 3.92%)		

Abbreviations: *PND* prophylactic central neck dissection, *TT* total thyroidectomy without prophylactic neck dissection, *LRR* locoregional recurrence rate, *RAI* radioactive iodine, *hypoPTH* hyypoparathyrodism, *Tg* thyroglobulin, *VFP* vocal fold paralysis, *OR* odds ratio

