##### Follow-up

All patients will have a postoperative visit within 4 months of the surgery with the surgeon to record post-op complications.

For all patients, Tg/LT4 and anti-Tg antibodies (anti-Tg Ab) measured 8 +/−2 weeks postoperatively, before stimulation with recombinant human thyrotropin (rhTSH).

At 8 +/− 2 weeks post-op before 131I:-Quality of life (SF-36) [47]-EQ-5D 3 Levels [48]-Anxiety (State-Trait Anxiety Inventory) [49]-Subjective dysphagia (measured via the SWAL-QOL questionnaire) [46]

For all patients (after 2 months but within 4 months postoperatively at the time of 131I administration:Stimulated usTg (Tg/rhTSH), anti-Tg antibodies (anti-Tg Ab)Neck ultrasoundWhole body scintiscan with SPECT performed 2–5 days after the RAI administrationQuality control of total thyroidectomy will be ensured by calculation of the % of 131I uptake, as an estimate of the size of thyroid remnant.

Further follow-up consists in:1 year after surgery (8 +/− 2 months after 131I) (primary endpoint): usTg on thyroxine treatment (usTg/LT4) with a standard ultrasensitive kit, anti-Tg Ab, neck ultrasoundYearly for 5 years (+/− 2 months after 131I): Tg/LT4, anti-Tg Ab, neck ultrasoundIf suspicious lesion (according to standardized criteria on ultrasound [52] > or = 8 mm (smallest dimension): indication for cytological examination by fine-needle aspiration biopsy (FNAB) and, for lymph nodes, for a determination the of level of thyroglobulin (Tg) in the needle washout fluidIf a suspicious lesion <8mm is visualized on ultrasound (according to standardized criteria,[52] cytology with FNAB (and Tg in the needle washout fluid) will be performed upon decision of the center’s principal investigators

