Functional evaluation and quality of life:Immediate postoperative complications (0–4 months after surgery) (hypoparathyroidism requiring supplementation, recurrent nerve paralysis visualized on systematic laryngoscopy)Complications at 1 year: treatment for persistent hypoparathyroidism, recurrent nerve paralysis visualized on systematic laryngoscopy performed at 1 yearAt 1 year after randomization: Subjective dysphonia (measured via the Voice Handicap Index [45]), Subjective dysphagia (measured via the SWAL-QOL questionnaire [46])Complete remission at 1, 3, and 5 years after randomizationAt 1, 3, and 5 years after randomization: Quality of life [SF-36 + EQ-5D], Anxiety (State-Trait Anxiety Inventory), all questionnaires in their validated French translation:Quality of life (SF-36) [47]EQ-5D 3 Levels [48]Anxiety (State-Trait Anxiety Inventory) [49]Subjective dysphonia (measured via the Voice Handicap Index, VHI) [45]Subjective dysphagia (measured via the SWAL-QOL questionnaire) [46]

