### Health Economics Analysis

A *cost-utility analysis* will be performed to compare total thyroidectomy to total thyroidectomy with bilateral prophylactic central neck dissection. The protocol used will be similar to the one used in ESTIMABL 1 trial and recently published in the Journal of Clinical Oncology [Borget I et al 2015]. The hypothesis is that TT alone and TTT + PND may differ in terms of the number of patients in complete remission at 1 year or in the number of patients requiring treatement of complications because of recurrent laryngeal nerve injury or hypoparathyroidism.

The horizon time will depend on the results obtained on the main criteria (1 year). If the study confirms the non-inferiority of TT versus TT + PND in terms of oncologic events, a horizon time of 1 year following the initial surgery will be considered.

Consequence will be expressed in QALYs (quality-adjusted life years). Utility score will be assessed using the EQ-5D questionnaire at baseline, 1, 3, and 5 years. QALY will be calculated by multiplying the length of time between two questionnaires by utility score.

Costs will be evaluated from the French collective perspective. Resources consumed by the patient’s management in each strategy will be collected prospectively at baseline, 1, 3, and 5 years.

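### The QALY calculation leaves out the 8-week EQ-5D that the trial collects, so on a 1-year horizon complications that resolve before 1 year add nothing to the QALY difference

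*Protocol article*

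**What the plan says.** The cost-utility analysis is described twice in the protocol article, under Outcomes: Cost-utility analysis and again under Health Economics Analysis. Both places give the same utility schedule: "Utility score will be assessed using the EQ-5D questionnaire at baseline, 1, 3, and 5 years". Both give the same rule: "QALY will be calculated by multiplying the length of time between two questionnaires by utility score". Both say that, if non-inferiority is confirmed, "a horizon time of 1 year following the initial surgery will be considered".

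The Follow-up section lists a further EQ-5D that appears in neither description: "At 8 +/− 2 weeks post-op before 131I:-Quality of life (SF-36) [47]-EQ-5D 3 Levels [48".

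The analysis supposes that the strategies may differ in 1-year remission or "in the number of patients requiring treatment of complications because of recurrent laryngeal nerve injury or hypoparathyroidism". Early events are recorded separately, as "Immediate postoperative complications (0–4 months after surgery". The Data collection subsections of both descriptions count hospital stays, consultations and procedures for managing complications as costs.

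**The concern.** On the 1-year horizon, the plan measures utility once before surgery and once a year later. Nothing in between enters the QALY, although an EQ-5D is taken inside the period in which early surgical complications are recorded.

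This matters because the background section names transient hypoparathyroidism as the possible extra morbidity of neck dissection, and Table 1 supports it, for example "Higher rate of temporary hypoPTH PND group 26% vs 10.8% (OR=2.56". The 1-year horizon applies when the arms have been found not to differ importantly in remission, so complications then become a main candidate source of any QALY difference. For those that resolve within the year, the plan would count the cost and leave out the loss of utility. Costs and effects in the incremental ratio would rest on different bases.

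**Working it through.** The article states no QALY figure, so there is none to reproduce. The check compares the QALY difference under the stated time points with the difference when week 8 is added.

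**Inputs**
- Time points in the plan: 0 and 1 year. Added point: t = 8/52 = 0.154 year.
- Temporary hypoparathyroidism: 26% with neck dissection and 10.8% without, from one meta-analysis of retrospective studies in Table 1. Excess = 0.26 − 0.108 = 0.152.
- Utility decrement per affected patient, d: not in the documents. Assumed range 0.05 to 0.20.
- Also assumed: equal baseline utility in the arms, every affected patient still affected at week 8, and full recovery by 1 year.

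**Stated plan (0 and 1 year)**
The arms have the same utility at both points. The difference is 0 whether the interval is multiplied by the mean, the starting or the ending score.

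**With week 8 added, trapezoid**
The week-8 value has weight t/2 + (1 − t)/2 = 0.5, whatever t is, so weeks 6, 8 and 10 give the same result.
Difference = 0.5 × 0.152 × d:

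| d | QALY difference per patient, in favour of thyroidectomy alone |
|---|---|
| 0.05 | 0.0038 |
| 0.10 | 0.0076 |
| 0.20 | 0.0152 |

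**Dependence on the course of recovery (d = 0.05 to 0.20)**
- Loss rises to week 8, then falls linearly to zero at 4 months (1/3 year): 0.152 × d × (1/3)/2 = 0.0013 to 0.0051.
- Full loss from surgery to week 8, then none: 0.152 × d × 8/52 = 0.0012 to 0.0047.
- Loss rises to week 8 and stops there: 0.152 × d × (8/52)/2 = 0.0006 to 0.0023.

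**Complications still present at 1 year, stated plan, per affected patient**
- Mean score: d/2, that is 0.025 to 0.10.
- Ending score: d, that is 0.05 to 0.20.
- Starting score: 0.

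Persistent complications are therefore counted under two of the three readings of the rule. Transient ones are counted under none.

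**The case against.** Several points on the other side carry weight.

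- **Persistent harm is captured.** A reader might infer that surgical complications in general carry no utility loss under this plan. The documents do not support that. Persistent hypoparathyroidism or vocal fold paralysis enters through the 1-year EQ-5D unless the starting score is used. Four rows of Table 1 report more permanent hypoparathyroidism with neck dissection, although the meta-analysis of randomised trials reports no difference. The stated hypothesis also names remission as well as complications.
- **The size is easily overstated.** Taking 0.05 as a mean loss over the whole neck-dissection arm would give 0.5 × 0.05 = 0.025 QALY. Table 1 points to an excess of 15.2 percentage points. At 0.05 per affected patient the result is 0.0038, about 6.6 times smaller.
- **The trapezoid has its own bias.** It assumes slow linear recovery from week 8 to 1 year. If the loss is full until week 8 and then ends, the trapezoid overstates it by 0.5/(8/52) = 3.25 times.
- **Some details may lie elsewhere.** The QALY rule is shorthand that does not exclude averaging the two scores. Averaging, actual dates and baseline adjustment can be left to an analysis plan, and the article says that the method resembles that of an earlier trial.
- **The consequence is limited.** This is a secondary analysis. If transient harm is greater with neck dissection, the omission makes a favourable result for thyroidectomy alone conservative. Planned one-way sensitivity analyses vary event incidence and utilities.

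These points limit the size and scope of the problem but do not remove it. The time points are stated explicitly in two places, and varying utilities in a sensitivity analysis does not put the patients' own week-8 values into the QALY.

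**Conclusion.** The concern holds in a limited form. The Follow-up section and the two cost-utility descriptions do not agree on which EQ-5D assessments exist for use. On the 1-year horizon, a complication that resolves before the 1-year questionnaire contributes zero to the QALY difference while its management cost is counted. If neck dissection causes more transient morbidity, the bias is against thyroidectomy alone.

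The effect is probably small: about 0.004 to 0.015 QALY per patient by trapezoid, and roughly 0.001 to 0.005 if recovery is complete by about 4 months. Every figure rests on an assumed decrement, on one retrospective meta-analysis for the rates, and on all affected patients still being affected at week 8. If only a fraction are, the figures shrink in proportion.

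The two-point problem is specific to the 1-year horizon. On a longer one the 3- and 5-year values enter, but the first year still lacks its week-8 value. The primary non-inferiority comparison is not affected.

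**What to change.** Add the EQ-5D at 8 ± 2 weeks to the utility schedule in both Outcomes: Cost-utility analysis and Health Economics Analysis. Replace the QALY sentence with a rule that fixes the calculation: area under the utility curve by trapezoid through baseline, 8 weeks and 1 year, then 3 and 5 years if the horizon is extended. Add one sensitivity analysis with faster recovery after week 8, for example reaching the 1-year value by the end of the 0–4 month complication window.

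The cost is a change of wording in two paragraphs and one extra analysis. The questionnaire is already scheduled, so patients face no added burden. The change should be fixed before the data are analysed. Two limits remain: linear interpolation from week 8 to 1 year may overstate short-lived losses, which the sensitivity analysis would show, and problems that resolve before week 8 are still missed.
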